## **10.0 RECORD AND SAMPLE MANAGEMENT**

### **10.1 Record keeping and handling**

The REDCap application located at the Telethon Kids Institute (TKI) will be used for study participants' record keeping and handling. This is a secure web-based application used within academia for the capture, management and storage of health research data. Access to the REDCap is via a 3-tiered access of username and password protected login system. Only research investigators who have been granted project permission to the REDCap database by project custodians will have access, allowing for security and confidentiality of data stored.

Access to the back-end server is restricted to authorised system administrators within the TKI. Secure access to the TKI is maintained via logged key-card entry with an additional key card entry for the server room. All system administrators have current Good Clinical Practice (GCP) accreditation.

It is intended that the summary of analysed data will be submitted for a publication in a peer reviewed journal. The identity of study participants in publications and scientific presentations will be anonymised.

### **10.2 Sample collection and shipping**

Each participant will be given a coded identifier, which will be attached to the participant source document. Only the coded identifier, the participant's initials and the collection date will appear on sample labels.

Sera obtained for the purpose of HI antibody measurement and nasopharyngeal swabs positive for Influenza A or B will be stored at -80°C. At the end of the influenza season the samples will be placed in biohazard bags and placed in boxes containing cool packs for shipment to the following address:

Peter Doherty Institute for Infection and Immunity  
[name]  
[name]  
[contact]  
[contact]

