### **3.4 Participant registration**

Each participant will be assigned a study ID number at the time of enrolment. All information collected during the research study will be de-identified. Re-identification will only be allowed for the CPI and AI's, and regulatory authorities at the time of the study audit.

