## **5.0 STUDY DESIGN**

### **5.1 Type of study**

This will be a prospective non-randomised, open label study.

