## **7.0 LABORATORY EVALUATIONS**

### **7.1 Assessment of humoral response to influenza vaccine**

Blood samples obtained for the purpose of the humoral response to the influenza vaccine assessment will be centrifuged and sera stored at -80°C. At the end of the influenza season, predicted to be in October, the samples will be sent to the Victorian Infectious Diseases Reference Laboratory (VIDRL) at the Peter Doherty

Institute for Infection and Immunity in Melbourne, Victoria. This centre is a WHO Collaborating Centre for Reference and Research on Influenza and is part of the WHO Global Influenza Surveillance Network organisation (WHO GISN).

HI antibody titers against each vaccine strain will be measured in each sample by standardised assay developed and updated by the WHO GISN (39).

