### **9.3 Statistical analysis**

The primary immunogenicity endpoints will be the percentage of participants achieving seroprotection and seroconversion. To assess if the extra vaccination dose improves immunogenicity, a McNemar test will be used to assess the

difference in these percentages as calculated from the immunogenicity status obtained after the last two doses of each individual. We will also evaluate geometric mean titers of HI antibodies at baseline and after vaccination. The geometric mean fold increase (GMFI), with 95% confidence intervals, will be calculated for each strain, using a log-normal approximation for the distribution of HI antibody levels pre and post vaccination.

Multivariate logistic regression models will be used to assess the influence of clinically relevant demographic and immunological variables to predict seroconversion to each influenza vaccine strain and complete seroconversion to all strains of the vaccine. Linear regression analyses of log-transformed HI antibody titers and log-transformed T-lymphocyte IFN- $\gamma$  levels will be undertaken to assess the influence of clinically relevant variables on humoral and cellular responses to vaccination, respectively.

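### Sample labels with participant code and collection date let a laboratory reader infer which serum follows the extra dose: an avoidable route to bias, of unknown size

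*Protocol*

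**What the plan says.** Protocol section 10.2 states what a tube carries: "Only the coded identifier, the participant's initials and the collection date will appear on sample labels". The same section describes batch dispatch: "At the end of the influenza season the samples will be placed in biohazard bags and placed in boxes containing cool packs for shipment". Section 5.2 spaces the visits four to six weeks apart. Section 5.3 sets three scheduled blood draws for participants aged 9 years or more and four for younger ones, with optional samples in between.

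The endpoint is read from these sera. Section 7.1: "HI antibody titers against each vaccine strain will be measured in each sample by standardised assay developed and updated by the WHO GISN". The reading is done at an external WHO collaborating centre. Section 9.3: "The primary immunogenicity endpoints will be the percentage of participants achieving seroprotection and seroconversion". The McNemar test then assesses the "difference in these percentages as calculated from the immunogenicity status obtained after the last two doses of each individual".

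Section 5.1 gives the design: "This will be a prospective non-randomised, open label study". The protocol mentions no masking of laboratory readers, no recoding of samples and no random testing order. On privacy, section 3.4 says: "All information collected during the research study will be de-identified".

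**The concern.** Each child is their own control, so the order of the samples plays the part that treatment allocation plays in a randomised trial. A label that links a child's sera and dates them lets a reader reconstruct that order. Both primary immunogenicity endpoints are thresholds applied to a laboratory reading: section 1.3 sets seroprotection at a titre of 40 or more, and seroconversion at a fourfold rise or a rise from below 10 to at least 40. A reading near a threshold that leans towards the expected answer would count as a benefit of the extra dose, and no concurrent group would show the same drift. Masked reading is a safeguard that an open-label, single-group design can still have.

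The labelling is not a detail left for later. Section 10.2 fixes it, and its wording leaves no room for a separate sample number.

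**Working it through.** **1. What the label reveals.** It carries code, initials and date, but no visit, dose number or age group. With the whole series in hand, the code groups a child's sera and the dates order them. The latest scheduled sample is the exit sample, normally the one after the extra dose. There are two exceptions. Optional samples add dates and can blur which serum followed the standard doses. A child aged 6 to 35 months who receives no third dose has a last sample that follows no extra dose (section 5.3).

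**2. The protocol's own power figures.** Inputs from section 9.2: discordance ψ, difference d, sample size n, alpha 0.05 (sidedness not stated; two-sided used). Power = Φ[(d√n − 1.96√ψ) / √(ψ − d²)].

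| n | ψ | d | Stated | Computed |
|---|---|---|---|---|
| 60 | 0.15 | 0.137 | 80% | 79.8% |
| 80 | 0.15 | 0.120 | 80% | 80.3% |
| 60 | 0.20 | 0.181 | 90% | 90.1% |
| 80 | 0.20 | 0.158 | 90% | 90.0% |

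The figures reproduce. Nothing here changes the sample size.

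**3. How many children decide the test.** 0.15 × 80 = 12 discordant children. Write b for those who improve after the extra dose and c for those who lose status. The uncorrected statistic is (b − c)²/(b + c), with critical value 3.84. The exact two-sided p is 2 × P(X ≤ c), X binomial with b + c trials and probability 0.5.

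Take 9:3 as a starting point chosen near the boundary. It is short of the effect the study is sized for, which at d = 0.12 implies b = 80 × (0.15 + 0.12)/2 = 10.8 and c = 1.2.

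- 9:3: 36/12 = 3.00; exact p = 2 × 299/4096 = 0.146.
- A child who lost status has the post-extra-dose sample read positive, giving 9:2: 49/11 = 4.45; exact p = 2 × 67/2048 = 0.065.
- A child negative at both times has the post-extra-dose sample read positive, giving 10:3: 49/13 = 3.77; exact p = 2 × 378/8192 = 0.092.

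One misread sample therefore crosses 3.84 only at 9:2 and only with the uncorrected statistic. Neither case is significant by the exact test.

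**4. Sensitivity to an assumed bias.** The protocol gives no misreading rate, so e is an assumption: the net share of all children, negative at both times, whose post-extra-dose sample is read up. With no true effect and ψ = 0.15, the chance of improving is 0.075 + e and of losing status 0.075. Enumerating all outcomes gives the probability of a significant false improvement:

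| e | n=80, exact | n=80, uncorrected | n=60, exact |
|---|---|---|---|
| 0% | 1.2% | 2.2% | 1.0% |
| 2% | 3.6% | 5.8% | 2.8% |
| 5% | 11.4% | 16.4% | 8.1% |
| 10% | 35.4% | 44.8% | 25.7% |

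A net bias near 2% matters little; 5% to 10% would matter. The documents do not say where in this range, if anywhere, the study would fall.

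**The case against.** The case against is substantial. The label names neither visit nor dose, so a reader would have to assemble a child's series and know the schedule. The titres are measured with a standardised assay at an external reference laboratory, not by the investigators. Batch dispatch already allows a child's sera to be tested together. A recoding step may sit in a laboratory manual that is not shown. Removing code and date from the tube makes the paired analysis depend on one linkage list.

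Most of this stands, and it limits the point to a low-severity one. It does not remove it: a standardised assay reduces discretion without being said to abolish it, and the protocol fixes the label without providing for recoding.

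Several stronger readings are tempting and not supported:

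- A reader might infer that the laboratory simply sees which sample follows the extra dose. The text supports only that it could usually be inferred. Open label describes treatment; it does not show that the laboratory is unmasked.
- A reader might infer that one borderline call overturns the trial, by comparing 9:3 with 10:2 (chi-square 5.33, exact p=0.039). That move keeps 12 discordant pairs, so it needs both samples of one child misread, in opposite directions.
- A reader might infer that ELISpot staff can look up visits because their institute hosts REDCap. Section 10.1 restricts access to investigators granted project permission, and ELISpot does not enter the McNemar test of section 9.3.
- A reader might take the initials as a clear breach of de-identification. Section 3.4 describes a coded scheme with limited re-identification, and initials do not necessarily identify a child. The tension is minor and separate from reader bias.

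**Conclusion.** The point holds as a cheap improvement. The labels fixed in section 10.2 let a reader usually infer dose order, which is the exposure in the primary within-child contrast, and the protocol states no step that prevents it. Both primary immunogenicity endpoints are therefore open to an avoidable bias. That such a bias would occur, or how large it would be, is not shown. The fragility figures rest on the protocol's 15% discordance with 80 participants and on a 9:3 split picked for illustration; the bias table rests on assumed misreading rates. No power figure, endpoint or analysis has to change.

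**What to change.** Amend section 10.2 so that, before shipment, each HI aliquot is relabelled with a random sample number that carries no participant code, initials or date. Hold the key linking that number to code, visit and date in REDCap, outside the reading laboratory. Ask the laboratory to test all of a child's sera in the same run and in random order, so that run-to-run differences do not fall between the two samples being compared. Release the key only after the titres are locked. Add one sentence to section 7.1 stating that readers are masked to sample sequence.

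The cost is a label template, a REDCap field and an agreement with the laboratory, with no extra visits or assays. The downside is that the linkage list becomes essential to the paired analysis, so it must be kept carefully and the relabelling checked.

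Separately, reconcile the initials on labels in section 10.2 with the de-identification statement in section 3.4.

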## **11.0 QUALITY CONTROL AND QUALITY ASSURANCE**

The project will be conducted in compliance with the protocol, Good Clinical Practice and regulatory requirements.

Influenza vaccines used during the study period will comply with the recommendations set by the ATAGI and approved by the NHMRC. All influenza vaccines used during the research study will be registered by the TGA.

## **12. ETHICAL AND REGULATORY CONSIDERATIONS**

### **12.1 Ethics**

The scientific content and clinical implications of the project will be considered by the Scientific Advisory Sub-Committee (SASC) prior to review by the Child and Adolescent Health Service (CAHS) Human Research Ethics Committee (HREC) and Research Governance Office (RGO).

### **12.2 Project monitoring**

The study investigators will permit project related monitoring, audits and regulatory inspections with a direct access to the source documents.

The study progress and results will be presented in a form of a report/presentation to the WACPCN Fellowship committee, the sponsor of the CPI. The study progress will be presented to the HOPAG during and at completion of the project to ensure relevant research outcomes are disseminated to the community. Study participants will receive a letter summarising the results of the research study once all data have been analysed.

## APPENDIX

### APPENDIX I

#### Adverse events following immunisation requiring reporting via the WAVSS system

|                                                            |                                                                                                                                                                                                                                                                                                                                                     |
|------------------------------------------------------------|-----------------------------------------------------------------------------------------------------------------------------------------------------------------------------------------------------------------------------------------------------------------------------------------------------------------------------------------------------|
| Abscess                                             | Occurrence of a fluctuant or draining fluid-filled lesion at the site of injection, with or without fever.                                                                                                                                                                                                                                          |
| Acute flaccid paralysis*                            | Acute onset of flaccid paralysis of one or more limbs following any vaccine.                                                                                                                                                                                                                                                                        |
| Allergic reaction (generalised)                     | A non-anaphylactic, generalised reaction characterised by 1 or more symptoms or signs of skin and/or gastrointestinal tract involvement WITHOUT respiratory or cardiovascular involvement.                                                                                                                                                          |
| Anaphylaxis                                         | A rapidly evolving generalised multi-system allergic reaction characterised by 1 or more symptoms or signs of respiratory and/or cardiovascular involvement AND involvement of other systems such as the skin or gastrointestinal tract.                                                                                                            |
| Arthralgia                                          | Joint pain without redness or swelling.                                                                                                                                                                                                                                                                                                             |
| Arthritis                                           | Joint pain with redness and/or swelling.                                                                                                                                                                                                                                                                                                            |
| Brachial neuritis                                   | Pain in arm causing persisting weakness of limb on side of vaccination.                                                                                                                                                                                                                                                                             |
| Death                                               | Any death of a vaccine recipient temporally linked to vaccination, where no other clear cause of death can be established.                                                                                                                                                                                                                          |
| Encephalopathy*                                     | An acute onset of major neurological illness temporally linked with vaccination and characterised by any 2 or more of the following 3 conditions: seizures, severe alteration in level of consciousness or mental status (behaviour and/or personality) lasting for 1 day or more, and/or focal neurological signs which persist for 1 day or more. |
| Encephalitis*                                       | Characterised by the above-mentioned symptoms and signs of cerebral inflammation and, in many cases, CSF pleocytosis and/or virus isolation.                                                                                                                                                                                                        |
| Extensive limb swelling                             | With or without redness which extends from the joint above to the joint below the injection site, or beyond a joint (above or below the injection site), or results in the circumference of the limb being twice the normal size.                                                                                                                   |
| Fever                                               | Only very high fever should be reported, e.g. >40.5°C.                                                                                                                                                                                                                                                                                              |
| Guillain-Barré Syndrome (GBS)*                      | Acute onset of rapidly progressive, ascending, symmetrical flaccid paralysis, without fever at onset of paralysis and with or without sensory loss. Diagnosed by cerebrospinal fluid investigation showing dissociation between cellular count and protein content.                                                                                 |
| Hypotonic–hypo responsive episode (shock, collapse) | The sudden onset of pallor or cyanosis, limpness (muscle hypotonia), and reduced responsiveness or unresponsiveness occurring after vaccination, where no other cause is evident such as a vasovagal episode or anaphylaxis. The episode usually occurs 1 to 48 hours after vaccination and resolves spontaneously.                                 |
| Injection site reaction (severe)                    | Reaction (redness and/or swelling) at site of injection which persists for more than 3 days AND is associated with ongoing symptoms such as pain or an inability to use the limb (see 'Brachial neuritis' above), and does not fulfil the case definition for extensive limb swelling and                                                           |

|                                                               |                                                                                                                                                                                                                                                                                                                                                                            |
|---------------------------------------------------------------|----------------------------------------------------------------------------------------------------------------------------------------------------------------------------------------------------------------------------------------------------------------------------------------------------------------------------------------------------------------------------|
|                                                               | requires hospitalisation.                                                                                                                                                                                                                                                                                                                                                  |
| Intussusception*                                       | The invagination of a proximal segment of bowel into the distal bowel lumen.                                                                                                                                                                                                                                                                                               |
| Lymphadenitis*
(includes suppurative lymphadenitis) | Occurrence of either at least 1 lymph node, 1.5 cm in diameter or larger, or a draining sinus over a lymph node.                                                                                                                                                                                                                                                           |
| Meningitis*                                            | Acute onset of major illness with fever and often neck stiffness/positive meningeal signs (Kernig, Brudzinski) and with CSF pleocytosis.                                                                                                                                                                                                                                   |
| Nodule                                                 | A discrete or well demarcated soft tissue mass or lump that is firm and is at the injection site in the absence of abscess formation, warmth and erythema.                                                                                                                                                                                                                 |
| Orchitis                                               | Swelling with pain and/or tenderness of testes.                                                                                                                                                                                                                                                                                                                            |
| Osteitis                                               | Inflammation of the bone due to vaccination.                                                                                                                                                                                                                                                                                                                               |
| Osteomyelitis                                          | Proven bacterial infection of bone.                                                                                                                                                                                                                                                                                                                                        |
| Parotitis                                              | Swelling and/or tenderness of parotid gland or glands.                                                                                                                                                                                                                                                                                                                     |
| Rash                                                   | Severe or unusual rash.                                                                                                                                                                                                                                                                                                                                                    |
| Screaming
(persistent)                              | The presence of crying which is continuous and unaltered for longer than 3 hours.                                                                                                                                                                                                                                                                                          |
| Seizure                                                | Witnessed sudden loss of consciousness and generalised, tonic, clonic, tonic-clonic, or atonic motor manifestations. 
 
• febrile seizures: with fever <math>\geq 38.5^{\circ}\text{C}</math>,
 
• afebrile seizures: without fever,
 
• syncopal seizures: syncope/vasovagal episode followed by seizure(s).
 
 |
| Thrombocytopenia                                       | Platelet count $< 50 \times 10^9/\text{L}$ .                                                                                                                                                                                                                                                                                                                               |
| Toxic shock syndrome*                                  | Abrupt onset of fever, vomiting, watery diarrhoea and shock within a few hours of vaccination which can be associated with other conditions listed here.                                                                                                                                                                                                                   |
| Vasovagal episode
(syncope, faint)                  | Episode of pallor and unresponsiveness or reduced responsiveness or feeling light headed AND occurring while vaccine being administered or shortly after (usually within 5 minutes), AND bradycardia, AND resolution of symptoms with a change in position (supine position or head between knees or limbs elevated).                                                      |
| Other severe or unusual events                         | Any unusual event that does not fit into any of the categories listed above, but is of medical or epidemiological interest, should be reported with a detailed description of the clinical features                                                                                                                                                                        |

\* Diagnoses must be made by a physician

